### Allocation, sequence generation, concealment and blinding

In this trial, site-stratified individual randomization will be generated centrally at WHO Headquarters. Participants will be randomly assigned to either control or experimental groups (allocation ratio of 1:1) as per a computer-generated randomization sequence in permuted blocks. All sites will receive identical treatment packs containing sufficient ampoules of dexamethasone or placebo for two full courses (in the event both initial and repeat treatments are needed) according to the randomization sequence, assembled consecutively in special dispensers (see Fig. 2). The assignment schedule will be stored at WHO.

**Fig. 2 Fig2:**
[figure not shown]
Study boxes and dispensers

Once eligibility is confirmed and consent obtained, trained study staff will randomize a woman by taking the next numbered treatment pack from the dispenser (which is designed to ensure packs are taken sequentially) (Fig. 2). A study pack contains sufficient ampoules for two full courses (in the event that both initial and repeat treatment are needed). The unique participant number is on the study pack (as a detachable sticker). Those women who complete the first course and have not given birth by 7 days will be reassessed for eligibility for a repeat course (which is the same as the initial allocation). Participants, care providers, study staff and outcome assessors will be blinded to the group allocation. Sealed code-break envelopes that contain each participant’s treatment allocation will be securely stored at the site for emergency unblinding only in the rare event that emergency unblinding is needed. All emergency code-break envelopes will be returned to WHO at the end of the trial.

### Data collection and management

Outcomes of interest are clinical and health service utilization outcomes. Data will be collected on standard paper forms, according to the trial Manual of Operations. Designated forms are available (if required) for adverse events, serious adverse events, protocol deviations or protocol violations. Data forms will also collect information on how many injections have been administered. Collected data will then be double-entered (at hospital or site level) into a web-based, GCP-compliant data management platform (Kamolo, Centro Rosarino Estudios Perinatales (CREP), Argentina), overseen by the site data managers. All data will be managed centrally by a trial data management team (CREP, Rosario, Argentina, and WHO, Geneva, Switzerland). A validation system has been built into the data management system to ensure consistency, accuracy and completeness of the data collected.

All study-related information will be stored securely at the study site. All participant information will be stored in locked file cabinets in secure rooms accessible only by designated study staff. All records that contain names or other personal identifiers will be stored separately from study records identified by participant number. All local databases will be secured with password protection. Participants’ study information will not be released outside of the study without the written permission of the participant.

### Statistical methods and analysis

The study statistician will be responsible for overseeing data management, as well as development of the statistical analysis plan and execution of the preplanned analyses (and any subsequent secondary analyses). The first version of the statistical analysis plan including dummy tables was finalized before recruitment began. The final statistical analysis plan will be agreed by the investigator group prior to completion of the trial and unblinding of participants.

For women, the intention-to-treat (ITT) population will be defined as all randomized women according to treatment assignment, regardless of compliance, excluding those withdrawing consent after randomization. However, if consent withdrawal is only for continuing to participate in the study, but not for using the data, then collected data for these participants will be included in the analysis. The per-protocol (PP) population will be all women in the ITT population excluding those with protocol violations that might affect the primary outcomes. For babies, similar populations will be defined according to their mothers.

The main analysis will be based on the ITT population, analysing all participants with outcome data available. Analysis of primary outcomes will be corrected for multiplicity (i.e. multiple primary outcomes). The primary outcomes of any baby death and maternal severe infection pertain to the ITT populations of babies and women, respectively. The primary outcome of neonatal mortality pertains to liveborn neonates only, within the ITT population of babies. We also plan to conduct a secondary PP analysis using the PP population defined above. The main population for the analysis of secondary outcomes will also be the ITT population. This analysis will also be corrected for multiplicity.

Baseline characteristics will be compared between groups to detect imbalances in prognostic variables that could bias the results. However, given the large sample size for the trial, randomization is likely to prevent any such imbalance. Numbers and baseline characteristics of women lost to follow-up will also be compared between study groups to detect any imbalances. Most study outcomes are binary variables, for which the number of participants, number of missing values and percentages by group will be reported. The intervention arm will be compared against the control arm for the primary outcomes using risk ratios with 95% CIs. Risk differences and two-sided *p* values will also be reported. The statistical technique used to conduct tests and obtain confidence intervals will be a logistic model with a binomial distribution and the log link to obtain relative risks. The identity link will be used to obtain risk differences. The stratifying variable of study hospital will be included in the model.

For continuous variables, the number of participants, the number of missing values, minima, maxima, means and standard deviations or medians, quartiles and interquartile range (IQR) by group will be reported as appropriate. The intervention arm will be compared against the control arm using mean differences and 95% CIs. The statistical technique used to conduct tests and obtain confidence intervals for this type of variable will be a general linear model with an appropriate distribution and including centre in the model as a stratifying variable.

Planned stratified analyses include by subgroups of type of preterm birth (planned preterm birth versus other), gestational age at randomization, gestational age at first dose, multiple and singleton pregnancy, study site/country, hospital capacity level, interval from time of randomization to birth, mode of delivery, and use of tocolytics. All models will be fitted using SAS Software version 9.3 (SAS Institute Inc., Cary, NC, USA). A separate model will be fitted for each primary outcome. Results will be reported according to Consolidated Standards of Reporting Trials (CONSORT) guidelines [31].

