### Hypotheses

We hypothesised that ACS use will result in clinical benefits for the baby without increasing the risk of harm to the mother. Therefore, we will apply a superiority hypothesis for the primary outcomes relating to neonatal death and any baby death, and a noninferiority hypothesis for the outcomes relating to maternal infection.

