### Intervention and control

WHO currently recommends that either dexamethasone or betamethasone (total 24 mg in divided doses) can be used for this indication; however, this trial will use dexamethasone on account of its wider availability, lower cost, and listing on the WHO Essential Medicines List. Dexamethasone sodium phosphate for intramuscular injection (4 mg/1 mL) will be used. The trial regimen is in line with WHO recommendations, namely: 1) a single dose of 6 mg intramuscular dexamethasone administered every 12 h, to a total of four doses (time points 0 h, 12 h, 24 h and 36 h) until course completion, discharge or birth (whichever comes first). If the full course is completed, the woman will receive a total of 24 mg in four divided doses; 2) if a woman has not delivered within 7 completed days after the first dose, is reassessed as eligible, and a subsequent clinical assessment demonstrates that birth is planned or expected in the next 48 h, a second course (repeat treatment pack) according to the regimen described above will be administered. The repeat course is an identical regimen to the first course, and is the same as the initial allocation (i.e. women initially randomized to dexamethasone will receive dexamethasone as repeat course and women initially randomized to placebo will receive placebo); and 3) a woman may have a maximum of two full courses only—no subsequent courses will be used even if delivery does not occur as expected or planned.

The control intervention is an identical placebo of normal saline, administered according to the same regimen.

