### Sample size

Sample size is calculated on the basis of the primary outcome of neonatal mortality at 28 completed days. A total of about 5416 women are needed to detect a reduction of 15% or more from 25% deaths to 21.3% among neonates from women who were administered ACS at < 34 weeks in a two-sided 5% significant test with 90% power. With 10% loss to follow-up, about 6018 women will need to be recruited.

Sample size has also been determined separately for the maternal infection primary outcome as a noninferiority hypothesis is required. A noninferiority hypothesis considers that the intervention is no worse than the comparator by more than a prespecified minimum difference (Δ). The prevalence of possible maternal bacterial infection for this trial is estimated at 10%, based on an assessment of rates of maternal infection-related outcomes in previous ACS efficacy trials [23]. The critical margin of noninferiority selected for this outcome is 2.5%, which represents a 25% difference from the baseline prevalence (10%) and is regarded as clinically relevant. Hence, under a noninferiority hypothesis a total sample size of 5024 women are needed (including 10% loss to follow-up) to demonstrate noninferiority within the 2.5% margin for the maternal infection outcome, assuming equal prevalence of 10% in the two arms, with a power of 80% and a significance level of 2.5%. It is important to note the relative importance of the three primary outcomes. If noninferiority of dexamethasone with respect to placebo is not demonstrated for possible maternal infection, this will need to be weighed against the effects (potential benefit) seen for the other two primary outcomes, which may be considered as having greater clinical significance.

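### For the maternal infection noninferiority outcome, ITT is the main analysis and per-protocol only secondary, so non-receipt and non-trial steroids favour the noninferiority conclusion

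*Protocol article*

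**What the plan says.** The Hypotheses section sets superiority for neonatal death and any baby death, and "a noninferiority hypothesis for the outcomes relating to maternal infection". Under Sample size, "The critical margin of noninferiority selected for this outcome is 2.5"%, on the risk-difference scale.

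Statistical methods and analysis then applies one ranking to all primary outcomes. ITT keeps every randomized woman in her assigned arm whatever her adherence, apart from consent withdrawals, and "The main analysis will be based on the ITT population, analysing all participants with outcome data available". The maternal outcome is expressly assigned to the ITT population of women. (That sentence calls it severe infection. I take it to be the possible bacterial infection outcome defined elsewhere.) The PP set removes women with protocol violations that could affect the primary outcomes, and its role is stated as: "We also plan to conduct a secondary PP analysis using the PP population defined above". The article does not say how an ITT result and a PP result that disagree would be read for the maternal outcome.

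On exposure, Intervention and control sets four doses from 0 h, given "until course completion, discharge or birth (whichever comes first"). Systemic corticosteroids from outside the trial, concurrent or within the past two weeks, exclude a woman at entry and again at the repeat-course check. The number of injections given is recorded.

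**The concern.** ITT does different work for the two kinds of hypothesis. If some women in the dexamethasone arm get no dexamethasone, or some placebo women get a corticosteroid elsewhere, the observed difference shrinks toward zero. For the deaths this makes a claim of benefit harder. For maternal infection it makes a claim of no important harm easier. This is why a noninferiority conclusion is usually asked to hold in both populations.

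The article shows some routes to dilution. Women are randomized when the pack is taken, at a point when birth is expected within 48 h. Some are discharged undelivered and are reassessed only if they return to a study hospital. The Background describes the drug class as widely used for this indication.

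The maternal outcome is one of the three primary outcomes and carries the maternal safety conclusion. The article itself cites a raised rate of suspected maternal infection in the earlier cluster-randomized trial as a reason for concern.

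**Working it through.** **1. Reproduce the plan's figure.** The inputs, from Sample size, are "assuming equal prevalence of 10% in the two arms, with a power of 80% and a significance level of 2.5"%, with margin 0.025. Taking 2.5% as one-sided:

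n per arm = (1.960 + 0.842)² × 2 × 0.10 × 0.90 / 0.025² = 2260.5, so 2261. The total is 4522, and 4522 / 0.90 = 5024.4.

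The article says "a total sample size of 5024 women are needed (including 10% loss to follow-up"). It reproduces.

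**2. Number available.** "With 10% loss to follow-up, about 6018 women will need to be recruited". The evaluable total is about 5416, or n = 2708 per arm.

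**3. Effect of dilution.** Two quantities are assumed, because the documents give neither: u, the share of the dexamethasone arm with no exposure, and c, the share of the placebo arm given non-trial steroids. The true rates with treatment as planned are set at 10% and 12.5%, exactly at the margin.

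- Placebo rate in ITT: pP = 0.10 + 0.025c
- Dexamethasone rate in ITT: pD = 0.125 − 0.025u
- SE = √[pP(1 − pP)/n + pD(1 − pD)/n]
- P(noninferiority declared) = Φ((0.025 − (pD − pP))/SE − 1.96)

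| u | c | Contrast lost | pP | pD | SE | P |
|---|---|---|---|---|---|---|
| 0 | 0 | 0 | 0.10000 | 0.12500 | 0.00858 | 2.5% |
| 5% | 0 | 5% | 0.10000 | 0.12375 | 0.00856 | 3.5% |
| 5% | 5% | 10% | 0.10125 | 0.12375 | 0.00858 | 4.8% |
| 10% | 5% | 15% | 0.10125 | 0.12250 | 0.00856 | 6.4% |
| 10% | 10% | 20% | 0.10250 | 0.12250 | 0.00858 | 8.4% |

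Putting the whole 20% loss on the dexamethasone side gives 8.5%, so the split hardly matters. With the 4522 women of the noninferiority calculation and the placebo rate held at 10%, losses of 5%, 10% and 20% give 3.4%, 4.5% and 7.8%.

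**4. Sensitivity to the true excess.** At a true excess of 3.0 points and 5416 women, a 20% loss gives an ITT difference of 0.03 × 0.80 = 0.024 and P = 3.3%. With no loss it is 0.6%. The effect is concentrated near the margin.

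**5. Price of requiring both populations.** Take no true difference, 10% in each arm, 2708 per arm and a share x excluded from PP.

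- ITT power = Φ(0.025/√(0.18/2708) − 1.96) = Φ(3.066 − 1.960) = 86.6%
- PP power uses 2708(1 − x) in place of 2708
- Joint power is bivariate normal with correlation √(1 − x), because PP is a subset of ITT

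| x | PP alone | Both |
|---|---|---|
| 5% | 84.8% | 83.6% |
| 10% | 82.9% | 81.4% |
| 15% | 80.7% | 79.1% |
| 20% | 78.3% | 76.6% |

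**The case against.** The strongest reply is that this belongs to the statistical analysis plan. The article already plans a PP analysis, a final plan is to be agreed before unblinding, and a rule for discordant results could well be there. That stands as far as the missing rule goes. A reader might infer that the PP result will be disregarded; the article does not say so. What it does state is the ranking itself: ITT main and PP secondary, with the maternal outcome expressly assigned to ITT.

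A reader might also infer that short courses dilute the comparison. They do not in the sense that matters here. A course ended by birth or discharge is the regimen as planned, is not a violation, and would remain in PP.

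Nor do the documents show that non-exposure is common. Dosing starts at 0 h, baseline data are collected after the first dose, monitors check remaining ampoules, and blinding removes knowledge of allocation as a reason to treat placebo women selectively. All of this stands, so the size can only be shown over an assumed range.

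It is also fair that ITT answers a legitimate question about assignment. Against that target, a diluted difference below 2.5 points is not a false claim. The figures above are therefore chances of declaring noninferiority when the excess with treatment as planned is at the margin. That quantity is still relevant, because the stated aim concerns safety when the drug is given.

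Finally, PP exclusions after randomization give up some comparability. This is a reason to require both populations, not to replace ITT.

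**Conclusion.** The point holds in a limited form. For a noninferiority outcome, the article fixes a population ranking suited to superiority, and the direction of the resulting distortion favours the claim. This is a stated choice, not merely an omitted detail.

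The size is modest and conditional. At the margin with 5416 evaluable women, the chance of declaring noninferiority moves from 2.5% to about 3.5%, 4.8% or 8.4% if 5%, 10% or 20% of the contrast is lost. It is smaller at larger true excesses. These figures rest on assumed losses, a 10% placebo rate and a normal approximation.

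A reader might go further and conclude that the maternal safety result will be biased, or that poor adherence is expected. The documents support neither. This is a risk that should be closed before unblinding, not a demonstrated bias.

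**What to change.** For possible maternal bacterial infection only, state in the final analysis plan that noninferiority is concluded when the upper confidence limit for the risk difference is below 2.5 points in both the ITT and the PP population. Keep ITT as the main analysis for both death outcomes.

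Replace the open PP definition, for this outcome, with a list of exclusions fixed before unblinding and applied without reference to whether or when infection occurred. Examples are no trial dose received, or any non-trial systemic corticosteroid after randomization. Limiting the steroid exclusion to use before infection onset would make the PP set depend on outcome timing and should be avoided. Any exclusion for missed doses needs the same care, since dosing halted because of infection would link exclusion to the outcome. Say explicitly that courses ended by birth or discharge after dosing began stay in PP.

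The work is wording only: the PP analysis is planned and injections are recorded. If the excluded women carry the dilution and their exclusion is unrelated to infection risk, the PP test brings the chance of passing at the margin back to 2.5% or less. The cost is joint power of about 81% with 10% excluded and about 79% with 15%, against about 87% for ITT alone and the 80% the plan set out to have. Beyond about 15% excluded, the loss is material and should be acknowledged.

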### Type of trial

The design is a multi-country, multi-centre, parallel, two-arm, double-blind, placebo-controlled trial of ACS for women at imminent risk of birth in the early preterm period. Women will be individually randomized (in a 1:1 ratio) to dexamethasone or placebo (normal saline). An individual randomization design was chosen as the intervention is at the level of the individual woman. The trial will test the superiority hypotheses regarding baby outcomes, and the noninferiority hypothesis regarding maternal outcomes, to 28 completed days after birth. The trial will be conducted in compliance with the trial protocol and good clinical practice (GCP) standards. This study protocol was developed in accordance with the Standard Protocol Items: Recommendations for Interventional Trials (SPIRIT) guidance [30]. See Additional file 1 for the SPIRIT checklist.

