### Participants

The populations of interest are: a) pregnant women (with confirmed live fetuses) from 26 weeks 0 days to 33 weeks 6 days gestation in whom birth is planned or expected within 48 h; and b) their fetuses and newborn babies. The inclusion criteria are: 1) birth planned or expected within 48 h^1^; 2) gestational age from 26 weeks 0 days to 33 weeks 6 days^2^ informed by ultrasound; 3) women with singleton or multiple pregnancies, where the fetus(es) is(are) alive; 4) women with no clinical signs of severe infection (as per clinical assessment)^3^; and 5) women willing and able to provide informed consent.

Women with a history of previous preterm birth, hypertensive disorders, a growth-impaired fetus, diabetes or HIV are eligible; comorbid conditions will be managed according to local guidelines.

The exclusion criteria are: 1) intrauterine fetal death; 2) identified major or lethal congenital fetal anomaly; 3) no prior ultrasound-based estimate of gestational age available and immediate ultrasound examination is not possible; 4) any concurrent or recent (within the past 2 weeks) systemic corticosteroid use during the current pregnancy (outside of the trial); 5) currently a participant in another clinical trial related to maternal and neonatal health; and 6) any other clinical indication where the treating clinician considers corticosteroids to be contraindicated.

A subset of participants may not give birth within 7 days of randomization. These women will be reassessed (upon representation to study hospital) for use of a repeat course. A repeat course will be used if 7 completed days have elapsed since the first dose of the first course, birth is planned or expected within the next 48 h, and the woman is still eligible according to the above criteria. In the event a woman with a multiple pregnancy requires a repeat course, the repeat course will be used if at least one fetus is alive.

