**Fig. 1 Fig1:**
[figure not shown]
SPIRIT figure for the Antenatal Corticosteroids for Improving Outcomes in preterm Newborns (ACTION)-I trial. ^1^ Data will be collected from randomized women from time of randomization to day 28 postpartum. Data will be collected on all newborn babies (single or multiple) from time of birth to day 28 postnatal or death. ^2^ Data will be collected from time of randomization. Some randomized women may be discharged without giving birth; however, data collection continues when they are readmitted later in the pregnancy for birth. ^3^ Data will be collected for women and newborn babies during admission until discharge. If the length of admission exceeds 28 days, data will be collected to 28 completed days only. ^4^ Women or newborn babies who experience a readmission to hospital during the follow-up period (postdischarge from hospital following birth) will have data collected. ^5^ Day 7 and day 28 follow-up visits will be performed, regardless of location (hospital or community). ^6^ The regimen is described in the study protocol. A full course (four doses) takes a total of 36 h to administer. In the event that a randomized woman does not give birth within 7 days, she may be eligible for a repeat course (four doses). ^7^ Baseline variables are collected after the first dose has been administered. Baseline variables include: age, education, marital status, gravidity, parity, maternal history of preterm birth, weight, height, mid-upper arm circumference, medical conditions (chronic hypertension, diabetes mellitus, HIV/AIDS, tuberculosis, pyelonephritis, anaemia, malaria), obstetric conditions (gestational diabetes, preterm prelabour rupture of membranes, pre-eclampsia or eclampsia, gestational hypertension, oligohydramnios, polyhydramnios, intrauterine growth restriction (known or suspected), macrosomia, abruptio placentae, placenta praevia, other obstetric haemorrhage), gestational, use of tocolysis, symptoms of imminent preterm birth. ^8^ All outcome variables are described in Additional file 2. IM intramuscular

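### The model named for the two baby primary outcomes makes no allowance for twins of the same mother, so their standard errors are somewhat too small if co-twins' outcomes are positively correlated

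*Protocol article*

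**What the plan says.** All of this is in the protocol article.

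- **Who is randomised.** Type of trial: the individual woman, 1:1. All babies of one woman are therefore in the same arm.
- **Who is eligible.** Participants: "women with singleton or multiple pregnancies, where the fetus(es) is(are) alive". The note to Fig. 1 adds: "Data will be collected on all newborn babies (single or multiple) from time of birth to day 28 postnatal or death".
- **Unit of analysis.** Statistical methods and analysis: "The primary outcomes of any baby death and maternal severe infection pertain to the ITT populations of babies and women, respectively". And: "The primary outcome of neonatal mortality pertains to liveborn neonates only, within the ITT population of babies". Both baby outcomes are thus counted per baby.
- **Model.** The same section: "The statistical technique used to conduct tests and obtain confidence intervals will be a logistic model with a binomial distribution and the log link", for relative risks, with the identity link for risk differences. Then: "The stratifying variable of study hospital will be included in the model". It names no random effect, estimating-equation approach or robust variance for mother. Multiples appear in that section only as a planned subgroup.
- **Sample size.** "A total of about 5416 women are needed to detect a reduction of 15% or more". The calculation is in women and does not mention multiples.

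**The concern.** An ordinary binomial likelihood takes its observations as independent given the terms in the model. Babies of one pregnancy share gestational age at birth, the cause of the preterm birth and the course of delivery, so a positive correlation in death is the natural expectation. Shared allocation and shared hospital do not count towards it, because both are already in the model. What matters is the correlation that remains.

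Because co-multiples always share an arm, positive residual correlation makes the naive standard error of the treatment effect too small. The direction of the error is therefore known: intervals too narrow and p values too small, for neonatal death and for any baby death. The estimate itself is not shown to be biased. What is at stake is a borderline result on a mortality outcome in a trial meant to inform WHO recommendations. A variance method chosen after unblinding would be open to criticism.

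**Working it through.** **Step 1. Reproduce the plan's own figure.** Inputs from Sample size: 25% deaths under placebo, a 15% relative reduction (0.25 × 0.85 = 21.25%, printed as 21.3%), two-sided 5%, power 90%, 10% loss.

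- Per arm, normal approximation: [1.960 × √(2 × 0.23125 × 0.76875) + 1.2816 × √(0.25 × 0.75 + 0.2125 × 0.7875)]² / 0.0375² = 2654.6.
- With continuity correction: (2654.6/4) × [1 + √(1 + 4/(2654.6 × 0.0375))]² = 2707.6, so 2708 per arm and 5416 in total.
- With loss: 5416 / 0.90 = 6018.

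Both stated figures reproduce exactly, as one independent binary observation per woman.

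**Step 2. Design effect.** Let m be the share of women with twins and ρ the within-pair correlation of death after hospital and arm. The share of babies who are twins is 2m/(1 + m), so under the independence model

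DE = 1 + ρ × 2m/(1 + m).

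The true standard error is √DE times the naive one. A nominal two-sided 5% test has true level 2 × [1 − Φ(1.96/√DE)].

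The document gives neither m nor ρ. Both are assumptions, shown over a range that includes the low end. Higher-order multiples are left out.

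Example, m = 10% and ρ = 0.5: 2m/(1 + m) = 0.2/1.1 = 0.182; DE = 1 + 0.5 × 0.182 = 1.091; √DE = 1.044; the interval is 1 − 1/1.044 = 4% too narrow; the level is 2 × [1 − Φ(1.96/1.044)] = 6.1%.

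Design effect, then true level of a nominal 5% test:

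| Twin pregnancies | ρ = 0.1 | ρ = 0.3 | ρ = 0.5 | ρ = 0.7 |
|---|---|---|---|---|
| 2% | 1.004; 5.0% | 1.012; 5.1% | 1.020; 5.2% | 1.027; 5.3% |
| 5% | 1.010; 5.1% | 1.029; 5.3% | 1.048; 5.6% | 1.067; 5.8% |
| 10% | 1.018; 5.2% | 1.055; 5.6% | 1.091; 6.1% | 1.127; 6.5% |
| 20% | 1.033; 5.4% | 1.100; 6.2% | 1.167; 7.0% | 1.233; 7.8% |

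The ratio of true to naive standard error runs from 1.002 to 1.111, so intervals are 0.2% to 10% too narrow (1 − 1/1.002 and 1 − 1/1.111).

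**Step 3. Does it affect the sample size?** 5416 women yield 5416 × (1 + m) babies, with effective number 5416 × (1 + m)/DE. This is at least 5416 as long as ρ ≤ (1 + m)/2. At m = 10% and ρ = 0.5 it is 5958/1.091 = 5461. Over the whole grid, power by the normal approximation without continuity correction is 0.898 to 0.942. The extra babies roughly pay for the correlation.

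**Step 4. Interim tests.** Interim analyses and stopping rules sets α = 0.001, two-sided, for the two baby outcomes but names no model. If the same model were used without clustering, the true level at m = 10% would be 0.0011 to 0.0019 over ρ = 0.1 to 0.7, and about 0.003 at m = 20% and ρ = 0.7.

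**The case against.** The strongest reply is that the article outlines the analysis and leaves the variance estimator to the statistical analysis plan. It never says that babies are treated as independent, that treatment and hospital are the only terms, or that model-based variance will be used. A first analysis plan existed before recruitment, and a final one is to be agreed before unblinding. The remedy keeps the distribution and links already stated.

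Part of this stands. Independence is implied by the named model and not stated in words, and the unseen plan may already deal with it. But the article is not silent. It gives the technique for tests and intervals, the links, the stratifying term and the software, and an analyst who followed it as written would obtain the naive variance. The planned subgroup by multiple and singleton pregnancy does not correct the main analysis.

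Three stronger readings do not hold:

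- **That the trial is too small because it counts women.** The 5416 and 6018 reproduce, and power is about unchanged (step 3).
- **That the trial's overall type I error exceeds 5% by the amounts in the table.** The article says the primary outcomes will be corrected for multiplicity. The table gives the level of a single test at nominal 5%, not the error rate of the whole trial.
- **That the stopping boundary is wrong.** The interim section names no model, and stopping is not to rest on statistics alone. The interim figures are conditional on the same model being used.

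The size is also open. Nothing in the document shows that co-multiples are strongly correlated, and with few twins or low correlation the inflation is almost nil.

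**Conclusion.** The point holds, at a modest size. As written, the named model gives standard errors that are too small for neonatal death and any baby death if co-multiples' outcomes are positively correlated after hospital and arm. On assumed inputs (2% to 20% twin pregnancies, correlation 0.1 to 0.7), the design effect is about 1.00 to 1.23 and a nominal 5% test has a true level of about 5.0% to 7.8%. The middle case, 10% twins and correlation 0.5, gives about 6% and intervals about 4% too narrow. Neither input comes from the document, so the direction is firmer than the size. It is worth settling before unblinding because two primary outcomes are involved and the correction is cheap, but a reader should not infer that the trial's conclusions would be invalid. Maternal infection is counted per woman and is unaffected.

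**What to change.** In Statistical methods and analysis, add that every per-baby model keeps its stated link (log for relative risk, identity for risk difference) and uses cluster-robust variance with the mother as the cluster. In SAS this can be done with generalised estimating equations (GENMOD with a REPEATED statement, mother as subject). With an independence working correlation, the point estimates are those of the planned model and only the variance changes. State in Interim analyses and stopping rules that any per-baby interim test uses the same variance. If the final analysis plan already says this, the published text need only be aligned with it.

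The cost is a sentence in each place, a line of code and slightly wider intervals. No new data should be needed, since the baby populations are already defined through their mothers. The sample size section can stay as it is.
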